### Study measures

2.6

#### Demographics and clinical characteristics

2.6.1

Demographics and clinical characteristics will be collected via REDCap and confirmed with chart review by the Study Coordinator ([name]) and second author ([name]) in ARIA (i.e., the electronic oncology information system). Data collected will include diagnosis and treatment details, sex, self-selected ethnicity and gender, employment status, annual family income, smoking status, alcohol consumption, and physical activity history.

#### Primary outcome: feasibility

2.6.2

To assess feasibility, we will track referral rate, enrolment rate, program adherence, measurement completion rate, and adverse events. All feasibility aspects of the triage clinic will be reported separately. All feasibility thresholds are based on feedback from the clinical team and other feasibility work in exercise oncology [[25], [26], [27], [28]]. With the advanced nature of disease in neuro-oncology, patients often experience high symptom burden and intensive treatments. Based on discussions with the neuro-oncology clinical team, lower feasibility thresholds (i.e., 50%) were expected for recruitment and adherence results in comparison to other tumour groups.

##### Referral to ACE-Neuro

2.6.2.1

To examine the feasibility of referral, the number of patients referred from the clinical team to ACE-Neuro will be tracked. The pre-determined threshold is ≥ 50%.

##### Enrollment into the study

2.6.2.2

To examine the feasibility of enrollment, the number of patients that enrol into the study after hearing the full study introduction will be tracked. The pre-determined threshold is ≥ 50%.

##### Program adherence

2.6.2.3

The number of participants that complete the exercise intervention will be tracked. The pre-determined threshold is ≥ 50%.

##### Measurement completion

2.6.2.4

Measurement completion rate, defined as the percentage of completed measures (PROs, functional fitness, objective physical activity levels) will be tracked. The pre-determined measurement completion is ≥ 60% for pre- and post-intervention assessments, and ≥40% at the two follow-ups (6 and 12 months).

##### Adverse events

2.6.2.5

To assess the safety of the intervention, all adverse events will be tracked and reported using a standardized adverse event reporting form, that ranks events as level 1 (minor incident with no lost time beyond day of injury; temporary, immediate care), level 2 (medical aid with no lost time beyond day of injury; medical care beyond first aid), and level 3 (serious injury or death).

#### Secondary outcome: preliminary effectiveness

2.6.3

To examine the preliminary effectiveness of the exercise intervention, PROs and assessments of functional fitness will be conducted. All measures were chosen based on their established validity, previous use in cancer patients, and relevance to the evaluation of the benefits of an exercise oncology program.

##### Patient-reported outcomes

2.6.3.1

Patient-reported outcomes (PROs) will include symptom burden, physical activity levels, quality of life, cognitive function, and fatigue. Symptom burden will be assessed using the revised Edmonton Symptom Assessment System (ESAS-r), which evaluates nine common symptoms experienced by cancer patients [29,30]. Self-reported exercise levels will be assessed using the modified Godin Leisure-Time Exercise Questionnaire (GLTEQ) [31] which reports mild, moderate, vigorous intensity and aerobic, resistance, and flexibility activities that last more than 10 min. Quality of life will be assessed using the Functional Assessment of Cancer Therapy-Brain (FACT-Br), which includes subscales for physical well-being, social/family well-being, emotional well-being, functional well-being, and additional neuro-oncology specific concerns, such as reporting seizures, speech difficulties, memory, etc. [32]. Cognition will be assessed using Functional Assessment of Cancer Therapy-Cognition (FACT-Cog), which includes subscales for perceived cognitive impairments [33]. Fatigue will be assessed using the Functional Assessment of Chronic Illness Therapy Fatigue Scale (FACIT-F) [34]. Finally, physical activity preferences will be collected from participants at baseline to help tailor their individual exercise prescription.

##### Assessment of functional fitness

2.6.3.2

Assessments of functional fitness will follow the set protocols within the larger ACE study [18], and are designed to be able to be completed in-person or via remote delivery (online assessment). All fitness assessments will be completed by an exercise specialist and will include assessments of body composition, muscular strength, muscular endurance, balance, flexibility, and cardiorespiratory fitness. Given the online nature for the start of ACE-Neuro, only the online assessments are indicated here. See Supplementary File 1 for a table of the in-person assessments. For online assessments, resting heart rate will be measured by the study-provided activity tracker or via manual palpation. Resting blood pressure will be measured if the participant has an at-home blood pressure monitor. Participants’ height and weight measurements from the triage clinic (Calgary) or their most recent medical appointment (Edmonton) will be used. Muscular endurance will be measured by the 30 s sit-to-stand test [35,36]. Static balance will be measured by the single-leg-stance following the Canadian Society for Exercise Physiology (CSEP) protocol [37,38]. Flexibility will be measured using the sit and reach test [39,40] and the shoulder flexion test [41]. Cardiorespiratory fitness will be measured using the 2-Minute Step Test [42].

##### Objective physical activity

2.6.3.3

Objective physical activity will be measured via the use of a consumer-level wrist-worn activity tracker (WAT; i.e., Garmin Vivofit 4). Garmin wearable activity trackers have high inter-device reliability of step count and are widely used across health research [43]. The Garmin activity tracker will be provided to all participants to objectively track physical activity habits throughout the intervention. Total weekly steps and physical activity minutes (i.e., mild, moderate, vigorous) will be tracked between baseline and week 12 of the program.

##### Qualitative interviews and photo elicitation

2.6.3.4

Qualitative data will be gathered across the study timeline via interviews and photo elicitation [44], to inform the feasibility of ACE-Neuro, as well as to assess outcomes associated with participation in the ACE-Neuro program (i.e., benefits, barriers, satisfaction, impact on well-being, impact on sense of self). All participants and their caregivers will be invited to a 45-60-min post-program interview, which will be recorded using [1]: a voice recorder if in-person or [2] end-to-end encrypted Zoom if remote. Participants will be interviewed within 2 weeks of completing the 12-week exercise program to limit recall bias, allowing them to reflect on their experience in the program. The interview guide is informed by the COM-B behaviour change framework examining participant *capabilities*, *opportunities*, *motivations*, and *behaviour* [24]. All healthcare providers and administrators involved in this work will also be invited for an interview to understand their clinical perspectives of ACE-Neuro implementation. The qualitative phase of this study will be guided by an interpretive description methodology and constructivist philosophy [45]. Interpretive description is well-established and has been used to guide numerous health-disciplined qualitative papers [[46], [47], [48], [49], [50], [51]]. With consent, patients who engage in this process will have candid photographs taken, and/or will be encouraged to take photos of their journey via their mobile device/personal camera, or a study-provided disposable camera. Standardized instructions for capturing photos will be provided to participants. Photos will be sent to the study team via the secure, end-to-end encrypted messaging app, Signal (https://signal.org/). When available, photos will be presented to the patient during the interviews to elicit memories and feelings. This can be a powerful tool to reinforce the nature of their exercise oncology program experience, and is a valid tool for aiding more in-depth understanding of the patient experience [44]. Photos gathered from and/or taken of patients will be transferred from the Signal App, study-provided disposable camera, or from the study team and stored on a secure University of Calgary server.

### Statistical analysis

2.7

#### Quantitative data

2.7.1

Descriptive characteristics of participants will be presented as mean ± standard deviation or percentages. Feasibility will be reported descriptively in relation to the pre-determined thresholds. We will investigate preliminary effectiveness of our secondary outcomes. Descriptive statistics will also be reported for feasibility numbers, PROs, functional fitness, and objective physical activity. Change scores will be calculated for PROs and functional fitness and to calculate power for a future fully-powered trial. Where available, the minimum clinically important difference (MCID) [52] will be reported as an indicator of clinical significance, which is appropriate for a pilot study.

#### Qualitative data

2.7.2

Interviews will be transcribed verbatim via ExpressScribe and coded in NVivo 12. As per an interpretive description methodology, the data will be inductively analyzed by two independent authors who will generate themes from the codes, followed by critical feedback from experts in qualitative research and exercise oncology.

## Discussion

3

The purpose of this pilot study is to assess the feasibility of a tailored exercise oncology program, ACE-Neuro, for individuals with primary brain tumours. The primary outcome of this study is to determine the feasibility of referral, enrolment, program adherence, measurement completion, and adverse events. The secondary outcomes include examining preliminary effectiveness of the neuro-oncology exercise program on patient-reported outcomes, functional fitness, and physical activity levels.

While exercise oncology programming is available for all tumour groups, patients with primary brain tumours remain underrepresented in the research process and underserved in exercise resources. By delivering one-on-one sessions, we hope this work will provide additional opportunities to participants that may have struggled in group-based settings that did not fully address their needs.

Findings from this work will be disseminated through academic channels (e.g., manuscripts, presentations), as well as through non-academic leveraging (e.g., knowledge translation initiatives such as patient group presentations, online resources for patients). Using an implementation framework approach (i.e., the RE-AIM framework; Reach, Effectiveness, Adoption, Implementation, Maintenance) [53], findings will target existing programs to improve resources, program delivery, and fine-tune models of care [54].

### Limitations

3.1

First, due to the smaller population of neuro-oncology patients, we may not have the power to determine effectiveness of the intervention on secondary outcomes (i.e., PROs, functional fitness). Instead, the feasibility and preliminary effectiveness findings of this study will be used to calculate the power for a future exercise trial in this population. Second, due to COVID-19, the delivery of our programming will initially be offered online, with the option of returning to in-person delivery once restrictions lift. Depending on participant preferences, we will continue to offer both options throughout the study duration. With the transition from online to in-person ACE-Neuro program delivery, we risk inconsistency in the results of our assessment of functional fitness. Nevertheless, the assessments that have been chosen can be replicated in both online and in-person settings with the same protocol in place.

Finally, due to the advanced natured of a brain tumour diagnosis and its associated treatments and side effects, it is important to note that some patients may not complete the full study intervention and measures, leading to lower adherence rates and poorer outcomes.

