### Timeline of assessments

2.5

In addition to attending the triage clinic, consenting patients will complete assessments at five timepoints (1): baseline PROs and health screening, pre-triage clinic, (2) baseline functional fitness, post triage clinic, (3) post-program (twelve weeks), (5) six months, (6) twelve months (Fig. 1). The twelve week, six month, and twelve month timepoints will all include the completion of PROs via REDCap and the assessment of functional fitness (online via Zoom or in-person). Objective physical activity will only be collected during the intervention (baseline to twelve weeks). Participants recruited in Edmonton will complete assessments at four timepoints, as they do not attend the triage clinic (i.e., baseline PROs and functional fitness occur at the same time for participants in Edmonton; Fig. 1).

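### Fitness may be tested online or in person under one supposed common protocol, but no strength test is named online, online Calgary weight is pre-program, and baseline mode need not be kept

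*Protocol article*

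**What the plan says.** The section on assessment of functional fitness (2.6.3.2) says the tests "are designed to be able to be completed in-person or via remote delivery (online assessment", and that they "will include assessments of body composition, muscular strength, muscular endurance, balance, flexibility, and cardiorespiratory fitness". It then explains that "only the online assessments are indicated here. See Supplementary File 1 for a table of the in-person assessments".

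The online tests it names are a sit-to-stand test for muscular endurance, a single-leg stance for balance, sit-and-reach and shoulder flexion for flexibility, and a step test for cardiorespiratory fitness. Resting heart rate is added, and blood pressure where the participant owns a monitor. For body size in online assessments, participants' "height and weight measurements from the triage clinic (Calgary) or their most recent medical appointment (Edmonton) will be used".

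The timeline of assessments (2.5) puts the Calgary triage clinic before the baseline fitness test. At twelve weeks, six months and twelve months it calls for "the assessment of functional fitness (online via Zoom or in-person".

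The limitations section (3.1) describes the change from online to in-person delivery and concedes that "we risk inconsistency in the results of our assessment of functional fitness". It adds: "Depending on participant preferences, we will continue to offer both options throughout the study duration". The sentence at issue closes that paragraph: "the assessments that have been chosen can be replicated in both online and in-person settings with the same protocol in place".

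The quantitative analysis section (2.7.1) plans change scores for functional fitness and links them to the power calculation for a later trial. The legend to Fig. 1 describes the study as single-arm.

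**The concern.** The reassurance in the limitations section is what allows online and in-person results to be pooled in one change score. If it fails for a domain, a participant tested in one mode at baseline and the other at follow-up has either no pair for that domain or a pair in which a measurement difference is mixed with real change.

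A control group measured in the same way would tend to cancel such a difference. Here there is none, so the offset stays in the mean change. Functional fitness is a secondary outcome, but its change scores are to be read against minimum clinically important differences where these exist and used to plan the next trial.

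**Working it through.** The article gives no sample size, switching rate, mode offset or standard deviation on this point, so there is no figure to reproduce. The check is mainly a comparison of the article's own statements.

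**Strength.** Section 2.6.3.2 lists six domains. Four (endurance, balance, flexibility, cardiorespiratory fitness) have a named online test. Body composition has only height and weight. Strength has nothing, because the sit-to-stand is assigned to endurance. If strength is tested in person only, that domain depends on mode and the sentence in 3.1 is too broad. If it is tested in neither mode, the domain list in 2.6.3.2 is wrong. The two sections need reconciling either way, and this does not depend on seeing Supplementary File 1.

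**Weight, online assessment in Calgary.** The source named is the triage clinic, and section 2.5 puts that clinic before the baseline fitness test. An online follow-up that uses the named source therefore carries the pre-program value forward: change = W(triage) − W(triage) = 0. If the value is not carried forward, the follow-up weight is missing and change cannot be estimated.

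**Mode switching.** Section 2.5 permits either mode at each follow-up and does not tie it to the baseline mode. Section 3.1 keeps both delivery options open by preference. A change score can therefore span two modes.

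**Illustration on assumed inputs.** Let a fraction q of participants switch mode, all in the same direction and independently of their true change. Let the new mode read m SD higher, with the SD of change set to 1. Then:

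- shift in mean change = q × m
- variance of change = 1 + q(1 − q)m²

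Suppose the true mean change is 0.3 SD and a future two-arm trial takes the observed mean change as its target difference (two-sided 5%, 80% power). Per arm, n = 2(1.960 + 0.842)² × variance / (0.3 + qm)². Without switching, n = 2 × 7.849 / 0.09 = 174.4, rounded up to 175.

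| q | m (SD) | shift (SD) | apparent change (SD) | n per arm |
|---|---|---|---|---|
| 0.1 | −0.3 | −0.03 | 0.27 | 218 |
| 0.1 | +0.3 | +0.03 | 0.33 | 146 |
| 0.3 | −0.3 | −0.09 | 0.21 | 363 |
| 0.3 | +0.3 | +0.09 | 0.39 | 106 |
| 0.5 | −0.3 | −0.15 | 0.15 | 714 |
| 0.5 | +0.3 | +0.15 | 0.45 | 80 |

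An offset of +0.5 SD would shift mean change by 0.05, 0.15 and 0.25 SD for the three values of q.

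If the future trial takes only the SD from this study and sets its target from a minimum clinically important difference, the effect is small. At q = m = 0.5 the variance is 1 + 0.25 × 0.25 = 1.0625, so n rises by about 6%.

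**The case against.** The strongest reply has four parts.

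- **The batteries may agree.** The in-person table is in Supplementary File 1, which is not shown. A reader might infer from the separate table that two different batteries are in use. The article does not establish that: the shared tests may follow one protocol, and 2.6.3.2 says they were designed for either mode. This stands. The mismatch is shown only for strength and for the online weight source.
- **The authors disclose the risk.** This also stands. The fault lies in the breadth of the sentence that follows the disclosure.
- **The bias has no established direction.** Because programming began online, a reader might infer a one-way drift that inflates improvement. But both options stay open by preference, a calendar trend over the recruitment period is not a switch within one person's twelve weeks, and nothing says which mode reads higher. An upward bias is not supported.
- **The outcome is secondary and reported descriptively.** The article admits limited power and does not say whether the future calculation will use the mean change or its SD. This limits the consequence but does not remove the contradiction.

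Analysis by mode may also be set out in the full protocol or analysis plan, so its absence here is not counted. That reply does not cover the strength domain or the weight rule, because the article states both itself. Nor can later analysis supply a measurement that was never taken.

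**Conclusion.** The point holds in a limited form. The statement that the chosen assessments run under one protocol in both settings does not fit an online list with no strength test. For Calgary participants whose follow-up is online, weight change from the named source is zero by construction or not estimable. Mode may change between baseline and follow-up, and in a single-arm design any offset enters the change score in full.

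The size of that offset cannot be derived from the article. The illustrated shifts (−0.15 to +0.15 SD for offsets of 0.3 SD either way) and the range of 80 to 714 per arm around 175 rest entirely on the assumed q, m and true change, and on the observed mean change being used as the target difference. Switches in opposite directions would partly cancel.

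A reader might also infer that no participant will have a post-program weight. That goes too far. In Edmonton the source is the latest medical appointment, which could fall after the program although it is not tied to the assessment date, and the in-person measures are not shown. Whether the in-person battery differs beyond strength cannot be verified.

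**What to change.** 1. Do the twelve-week fitness test, and those at six and twelve months, in the participant's baseline mode where restrictions and preference allow.
2. Record the mode at every fitness assessment.
3. Report change scores for same-mode pairs alongside those for all pairs, and show switched pairs separately. Switched pairs need not be discarded.
4. For participants assessed online, obtain a weight at each follow-up, or do not report body-composition change for them.
5. State that strength is not assessed online, and report strength change only where it was tested in the same way at both times.
6. Limit the closing sentence of that paragraph in 3.1 to the tests common to both modes, so that it agrees with 2.6.3.2.

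The cost is one extra field in REDCap, a scheduling preference, a follow-up weight for online participants and some rewording. The drawback is that same-mode subsets will be smaller in an already small cohort (the article expects about 25 to 30 eligible patients per site per year), which is why the all-pairs result should stay alongside. Forcing a mode against restrictions or a participant's choice is not proposed.

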## Conclusion

4

Patients with primary brain tumours are a clinically underserved patient population that are underrepresented in the exercise oncology research. To address this gap, ACE-Neuro is a tailored exercise oncology program that will be implemented into the clinical care pathway across Alberta. ACE-Neuro provides an opportunity to provide patient-centered supportive cancer care that enhances wellness for individuals living with a brain tumour diagnosis.

## Study registration

This study was pre-registered at Clinical Trials.Gov. Clinical Trials Registration Number: NCT04831190 (https://clinicaltrials.gov/ct2/show/NCT04831190).

## Data Availability

Data will be made available on request.
